## Abstract

**Background:**

Mild traumatic brain injury or concussion is a global public concern, with an estimated annual incidence between 48 million and 96 million worldwide. It is a socioeconomical problem, and almost one-third of individuals with concussion suffer from severe persistent post-concussive symptoms (PPCS), with an increased risk of unemployment or terminating their studies. To date, no single treatment is available with guaranteed success. Creatine monohydrate (CrM) has shown potential as a treatment for post-concussive symptoms, having a positive impact on cognitive function, chronic fatigue, depression, and anxiety. The aim of this study is to examine the effect of CrM on PPCS assessed using the Rivermead Post-Concussion Symptoms Questionnaire (RPQ).

**Methods:**

The study is designed as a double-blinded randomised controlled trial. Study participants are found through neurological outpatient clinics in Denmark or through social media. They will be between 25 and 35 years of age, will have suffered from PPCS for 6–12 months prior to inclusion, and will have no comorbidities. The participants will be randomly allocated to either an intervention group (INT), placebo group (PLA), or control group (CG). Baseline data will be collected immediately after inclusion, and the study period will be 7 weeks. Follow-up data will be collected 1 week after the end of the study period. The primary outcome of the study is changes in RPQ score. Changes in weight and training status will be adjusted for as potential confounders.

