## Methods and analysis

### Study design

The pilot study will be performed as a randomised controlled trial in accordance with the SPIRIT guidelines (30). The study will include a convenience sample of 45 patients. The patients will be randomly allocated to either a control group (CG), placebo group (PLA), or intervention group (INT), with 15 patients in each group. As there has been too few randomised controlled trials (RCT) to establish a sample size through power calculations, this pilot study will be used to establish a sample size for a future RCT.

The study will be double blinded, that is, the participants, staff and investigators, will be unaware of treatment group the patients are allocated to. Furthermore, the process of randomisation will consist of a nutritionist not otherwise associated with the study who will randomly allocate each participant to a group until the desired sample size is reached. The nutritionist in charge of this step will also distribute either the placebo or the CrM to the participants in each of these groups.

CG will not receive any treatment other than usual treatment. PLA and INT will both receive a powder that must be ingested. PLA will receive a powder similar in appearance to CrM, but with no apparent nutritional value. INT will receive CrM.

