### Potential confunders

Body weight will be measured at baseline, halfway through the intervention, and 1 week after the end of the intervention. These measurements are performed to ensure that changes in body weight do not affect the results, as changes in body weight are common with CrM supplementation.Physical activity will be self-reported in hours/week throughout the study period, as this can be a relevant factor to measure.

In the pilot study we will not assess the risk factors, but in the future RCT study, we will assess generally accepted risk factors.

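### Adjusting the between-group RPQ comparison for post-randomisation changes in weight and training means the estimate may not be the total effect of allocating CrM

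*Protocol article*

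**What the plan says.** The Methods part of the abstract commits to the adjustment: "Changes in weight and training status will be adjusted for as potential confounders".

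The section on potential confounders gives the timing and the reason. On timing: "Body weight will be measured at baseline, halfway through the intervention, and 1 week after the end of the intervention", and "Physical activity will be self-reported in hours/week throughout the study period". On the reason for weighing participants: "to ensure that changes in body weight do not affect the results, as changes in body weight are common with CrM supplementation".

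The Statistics section names linear mixed regression for the comparison between groups and lists no covariates. It neither repeats nor withdraws the adjustment. Nothing in the article restricts the adjustment to baseline values or calls it secondary, exploratory or a mediation analysis.

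The design is a randomised three-arm pilot (INT, PLA, CG), "with 15 patients in each group". The primary outcome is change in RPQ score.

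**The concern.** A confounder is a common cause of treatment and outcome. Random allocation removes such causes apart from chance imbalance, and chance imbalance lies in baseline values, not in later changes. A change in weight during the intervention comes after allocation. The article's reason for worrying about it, "as changes in body weight are common with CrM supplementation", is the reason not to condition on it: it marks weight change as something the treatment may produce.

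Conditioning on such a variable can do two things. If weight change carries part of any effect on symptoms, that part is removed from the INT coefficient. If weight change and recovery share other causes, such as appetite, mood or activity, conditioning links allocation to those causes and breaks the balance that randomisation gave. In either case the coefficient answers a different question from whether allocating CrM changes RPQ.

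Change in training has the same timing. Hours could rise because symptoms ease, and adjustment would then remove some of the benefit. That is inference, because the article does not say that CrM alters training.

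What is at stake is the meaning of the between-group result on the primary outcome.

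**Working it through.** The article states no effect size, SD or correlation for RPQ or weight, so there is no figure of its own to reproduce. The question is how far adjustment could move the estimate.

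**Inputs from the article.** 15 patients per arm, 3 × 15 = 45; weight change is common with CrM (no size given); outcome is change in RPQ.

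**Assumptions, not in the article.** d = INT minus PLA difference in weight change, in within-arm SDs, tried at 0.5, 1 and 1.5. rho = within-arm correlation of weight change with RPQ change, tried from −0.3 to 0.5. RPQ change has within-arm SD 1. CrM alone shifts weight. One change score per patient stands in for the repeated measures.

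**Shift.** Let I = 1 for INT and 0 otherwise, and let tau be the total effect. Write weight change as W = d·I + u and RPQ change as Y = tau·I + rho·u + error. Substituting u = W − d·I gives Y = (tau − rho·d)·I + rho·W + error. The adjusted INT coefficient is tau − rho·d, so the shift is −rho × d.

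**Precision.** The unadjusted INT−PLA standard error (SE) is sqrt(2/15) = 0.365 SD. Adjustment multiplies it by about sqrt((1 + d²/4)(1 − rho²)) in a two-arm model, or sqrt((1 + d²/6)(1 − rho²)) with one slope pooled over three arms. The first factor is the cost of collinearity with arm; the second is the gain from explaining outcome variance.

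| d | rho | Shift (SD) | SE factor, two arms | SE factor, three arms |
|---|---|---|---|---|
| 0.5 | 0 | 0 | 1.03 | 1.02 |
| 0.5 | 0.3 | −0.15 | 0.98 | 0.97 |
| 1 | 0 | 0 | 1.12 | 1.08 |
| 1 | 0.2 | −0.20 | 1.10 | 1.06 |
| 1 | 0.3 | −0.30 | 1.07 | 1.03 |
| 1 | 0.5 | −0.50 | 0.97 | 0.94 |
| 1.5 | 0.3 | −0.45 | 1.19 | 1.12 |

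A negative rho reverses the sign of the shift and leaves the SE factor unchanged. In the three-arm model the adjusted SE becomes the smaller one once the absolute value of rho exceeds sqrt(1 − 1/(1 + d²/6)): 0.20 at d = 0.5, 0.38 at d = 1 and 0.52 at d = 1.5.

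**Simulation check.** Three arms of 15, 6,000 runs per setting, true total effect −0.50 SD. At d = 1 the mean adjusted estimate was −0.80 for rho = 0.3, −0.20 for rho = −0.3 and −0.50 for rho = 0. The unadjusted estimate averaged about −0.50, with SD about 0.36, in every setting.

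**The case against.** The strongest reply is that the harm is conditional. Without a within-arm association between weight change and RPQ change there is no shift, and the article gives no evidence on that association. This stands, and it limits the claim to what may happen. It does not rescue the adjustment. The stated purpose, "These measurements are performed to ensure that changes in body weight do not affect the results", allows that weight change may be related to the outcome, and if it is unrelated there is nothing to adjust for.

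A reader might infer that the adjusted effect is certainly biased and certainly less precise. The article supports neither. The table shows settings with no shift, and settings where the SE falls. The largest collinearity penalty belongs to rho = 0, where the shift is zero, so the worst precision figure and the shift figures should not be quoted together.

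A reader might also infer an inflated type I error. Simulated rejection rates with no total effect and 15 per arm in a two-arm comparison are about 8% (d = 1, rho = 0.2), 11% (d = 1, rho = 0.3) and 16% (d = 1.5, rho = 0.3). They rest on the assumed values and on rho arising from common causes. If weight change itself acted on symptoms, a zero total effect would require an opposing direct effect, and the adjusted test would be detecting something real.

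Three smaller points carry weight:

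- The abstract's phrase could be read as changes in weight, plus training status as such, so the textual support is firm for weight only.
- Cohen's d is to be derived from mean differences and SDs with no adjustment mentioned, so it does not follow that the next trial's planning figure would come from the adjusted model.
- This is a pilot with an unadjusted SE of 0.365 SD; a shift of 0.30 SD is 0.30/0.365 = 0.82 of one SE. The shift is systematic, though, and would not shrink with more patients.

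An article may leave model detail to an analysis plan, but that does not answer the point: the abstract states this choice rather than leaving it open.

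**Conclusion.** The concern holds in conditional form. The abstract plans to adjust the randomised RPQ comparison for a change that the article itself says is common with the treatment. The adjusted INT coefficient may therefore differ from the total effect of allocating CrM by about −rho × d SD of RPQ change, in a direction that cannot be known in advance. Over the assumed range d = 0.5 to 1.5, with rho at most 0.3 in absolute value, the shift runs from zero to 0.45 SD. No claim about precision can be made in either direction. For training, the document supports only that the change is post-randomisation; an effect of CrM on training, or of symptom relief on training, is plausible but not stated.

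**What to change.** Four changes of wording:

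1. State that the main between-group mixed model for RPQ contains no covariate measured after randomisation.
2. If adjustment is wanted, use baseline RPQ, baseline weight and baseline training hours. All three are already collected at the Pre visit in Table 1.
3. Report changes in weight and training by arm descriptively, or analyse them in a mediation analysis labelled exploratory, with its assumptions stated.
4. Align the abstract, the section on potential confounders and the Statistics section. The Statistics section names no covariates, so it needs the model stated rather than a sentence removed.

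The cost is a few sentences. No new data, visits or patients are needed.

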**Ethics and dissemination:**

This protocol is approved by the National Committee on Health Research (97508) and by the Danish Data Protection Agency 11.651. The investigators intend to submit their study findings for publication in peer-reviewed journals and disseminate the findings via presentation at academic meetings/conferences.

**Clinical Trial registration**: NCT05562232, registered September 30, 2022.

## Introduction

Mild traumatic brain injury (mTBI), which is used interchangeably with ‘concussion’ in the literature (1), is a significant public concern. It is estimated that between 0.6 and 1.2% of the general population will suffer an mTBI each year (2, 3), which represents 48–96 million people on a global scale. Of these patients, an estimated 10–30% will suffer from persistent post-concussive symptoms (PPCS) (4, 5). These symptoms typically include headache, poor concentration, memory problems, fatigue, sleep difficulties, dizziness, irritability, and feeling nervous or anxious (4, 6). PPCS is not only a health problem, but also a socioeconomical problem (7). Data from Fallesen et al. (7) revealed that the salary of a concussion patient in Denmark 5 years after their concussion decreased 4.2% and was associated with an increased risk of becoming unemployed. To date, no single treatment option has been made available with guaranteed success; therefore, nutritional supplements represent an alternative.

The nutritional supplement creatine monohydrate (CrM) is one of the most popular ergogenic aids on the market among professional and amateur athletes (8). It is mostly used in the development of muscle mass, as creatine is primarily found in skeletal muscle (9). Roughly 5% of the body’s creatine is distributed in the brain and testicles (9). As mTBI alters the metabolism of the brain (10–12), creatine supplementation might be beneficial for patients with PPCS (13). Although studies have shown little evidence for alterations in brain creatine in the acute phase (13). This is further supported by a study suggesting that creatine supplementation may reduce the severity of mild concussion in animal models (14).

Furthermore, because the enzyme creatine kinase (CK), which is involved in the ATP energy system, also has a brain specific isoform (BB-CK) (15), creatine may be a relevant component the energy system of the central nervous system (16). In addition, several studies suggests that creatine supplementation increases cellular energy availability (17). Creatine has been reported to increase brain phosphocreatine content by as much as 15%, which in turn improves the metabolic processes of the brain (14, 18–21).

CrM has been described to be a potent anti-inflammatory molecule (22, 23). It has been shown to reduce cytotoxic effects in cells that have undergone oxidative injury without affecting antioxidant enzyme activity (23), and it has also been shown to inhibit the reactive oxygen species-induced formation of mitochondrial permeability transition pores in the liver mitochondria of mice (22). Moreover, concussion seems to increase inflammation in the brain (24), and this inflammation has been hypothesised to correlate with the symptomatology and duration of the concussion (25). Even though research in the area of recovery is scarce, neuroinflammation seems to play a vital role in the pathophysiology of concussions (24). This warrants hopes of a decrease in post-concussive symptoms following CrM supplementation.

Other studies have indicated that CrM improves cognitive function, including fatigue (26), working memory (27, 28), and mood state (17), which are all symptoms associated with PPCS (4). Additional evidence suggests that creatine supplementation can help with chronic fatigue (17), depression (29), and anxiety (17). Therefore, CrM may be helpful in the treatment of PPCS.

Currently, there is no viable treatment option for PPCS patients. However, if CrM supplementation shows positive results, patients suffering from PPCS would be able to reduce their symptoms in a relatively easy and low-cost way.

*The aim* of this study is to investigate whether CrM as a supplement reduces the number and severity of symptoms in patients with PPCS through self-reported post-concussion symptoms questionnaires.

## Methods and analysis

### Study design

The pilot study will be performed as a randomised controlled trial in accordance with the SPIRIT guidelines (30). The study will include a convenience sample of 45 patients. The patients will be randomly allocated to either a control group (CG), placebo group (PLA), or intervention group (INT), with 15 patients in each group. As there has been too few randomised controlled trials (RCT) to establish a sample size through power calculations, this pilot study will be used to establish a sample size for a future RCT.

The study will be double blinded, that is, the participants, staff and investigators, will be unaware of treatment group the patients are allocated to. Furthermore, the process of randomisation will consist of a nutritionist not otherwise associated with the study who will randomly allocate each participant to a group until the desired sample size is reached. The nutritionist in charge of this step will also distribute either the placebo or the CrM to the participants in each of these groups.

CG will not receive any treatment other than usual treatment. PLA and INT will both receive a powder that must be ingested. PLA will receive a powder similar in appearance to CrM, but with no apparent nutritional value. INT will receive CrM.

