### Procedure

As both PLA and INT are the interventions, they will follow the same protocol for ingestion: 5 g per day for 7 weeks. All 5 g will be ingested at once (9). This protocol has been chosen instead of the more common 0.3 g/day for the first week ingested five times during the day (9). In other studies on CrM and the brain, 5 g per day was also the chosen strategy (31, 32). However, studies on CrM in the muscles indicate that both protocols illicit the same response at 28 days (9), and a loading phase is not required (33). Furthermore, some studies have used this protocol with creatine supplementation and reported increased cognitive function (27, 34). Our reason for choosing 5 g/day over 7 weeks was to increase compliance and decrease the risk of discomfort with high CrM intake. An intake five times a day for the first week is demanding and would likely result in some participants quitting the study.

At the mid-phase of the study, all baseline measurements will be repeated. The length of the intervention is 7 weeks. After the 7 weeks, all baseline measurements will be repeated (see Table 1). One week after last ingestion, the measurements will be performed one last time. At the week 8 appointment, every participant will be asked whether they thought they had received a placebo or CrM to determine how large an effect the placebo will have on the results.

**Table 1 tab1:** Study timeline.

	Pre (−1 week)			Intervention (7 weeks)			Post (+1 week)		
	CG	PLA	INT	CG	PLA	INT	CG	PLA	INT
Declaration of consent	X	X	X						
Height (m)	X	X	X				X	X	X
Weight (kg)	X	X	X	X	X	X	X	X	X
Concussion history	X	X	X						
Training status (hours/week)	X	X	X				X	X	X
RPQ (35, 36)	X	X	X	X	X	X	X	X	X
CrM						X			
Placebo powder					X				
Usual treatment				X	X	X			

CG will receive standard care. However, to our knowledge there is no commonly accepted description of standard care for PPCS in the literature. In general, these participants will be advised to continue with daily regular routines during the 7 weeks.

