### Statistics

Scales will be assessed for internal reliability, and Cronbach’s alpha will be estimated. We will apply unpaired t-tests to assess mean score differences at baseline and chi-square tests for sex distribution. Differences over time will be explored using paired sample t-tests. Applying Cohen’s d, effect sizes will be derived by calculating mean differences and standard deviations. To assess differences in outcomes between groups, we will employ linear mixed regression. All statistical analyses will be performed using SPSS for Windows (IBM Corp., 2018., Version 25.0., Armonk, NY).

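### The trial is called double blind throughout, but the control group takes no powder; blinding is possible only for INT versus PLA, and that contrast should carry the CrM conclusion.

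*Protocol article*

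**What the plan says.** The abstract (Methods) describes a double-blinded randomised trial. Study design spells this out: "the participants, staff and investigators, will be unaware of treatment group the patients are allocated to". The statement covers all three groups.

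The same section then describes treatments that differ visibly. On the control group: "CG will not receive any treatment other than usual treatment". On the other two: "PLA and INT will both receive a powder that must be ingested", with the placebo made to look like CrM. Table 1 agrees: CrM is marked for INT, placebo powder for PLA, and neither for CG.

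Under Procedure, at the week 8 appointment, "every participant will be asked whether they thought they had received a placebo or CrM".

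On the outcome: "The primary outcome of the study is changes in RPQ score". Under Outcomes, patients rate each of the 16 RPQ symptoms from 0 to 4 themselves.

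On the analysis, the Statistics section says: "To assess differences in outcomes between groups, we will employ linear mixed regression". It gives no reference group and does not say which of the three pairwise comparisons answers the question about CrM. The aim (end of the Introduction) and the hypothesis (Discussion) speak of CrM reducing symptoms without saying compared with what.

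**The concern.** A participant who is given nothing to ingest knows that they are in CG. A participant who is given powder knows that they are not. The blinding statement is therefore untrue for every comparison that involves CG.

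This matters because the outcome is a self-rating, so what patients expect can move the score directly. INT-PLA holds expectancy roughly equal in the two arms. INT-CG does not: it contains any effect of CrM, plus the effect of knowingly taking a possible remedy, plus any disappointment in CG.

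The wording does not lead a reader to INT-PLA. The open arm is the one labelled control group, and the Procedure section refers to PLA and INT together as the interventions. An intervention-versus-control reading of the results would land on the unblinded comparison while the paper describes the trial as double blind. The pilot is also meant to set the sample size of a later trial, so an effect size taken from INT-CG would carry expectancy into that calculation.

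**Working it through.** **1. Can the blinding statement be true?**

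| Group | Powder | Can the participant be unaware? |
|---|---|---|
| CG (15) | none | No: knows they are in CG |
| PLA (15) | placebo | Only as to PLA or INT |
| INT (15) | CrM | Only as to PLA or INT |

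The protocol's total reproduces: 3 × 15 = 45. CG is 15/45, one third of the sample. Of the three pairwise comparisons, INT-PLA can be blind; INT-CG and PLA-CG cannot.

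The week 8 question shows the same slip. It goes to everyone, but the only answers it names are placebo and CrM, and CG participants took neither.

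**2. What each contrast estimates.** Let c be the effect of CrM over placebo and e the expectancy effect of taking a powder, both as improvements in RPQ in SD units.

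- INT-PLA = (c + e) − e = c
- PLA-CG = e
- INT-CG = c + e

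If c = 0, INT-CG equals e.

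**3. Size of the risk, as an illustration.** From the document: 15 per group. Assumed, because the document does not give them: two-sided alpha 0.05, a normal outcome, a t-test at one time point, c = 0, and e from 0.2 to 0.8 SD.

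The chance of a significant result favouring INT is P(T > t₀.₉₇₅,₂₈), where T is noncentral t with 2 × 15 − 2 = 28 degrees of freedom and noncentrality d × √(15/2) = 2.739d. For INT-CG, d = e. For INT-PLA, d = 0.

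| Assumed e (SD) | Noncentrality | INT-CG favours INT | INT-PLA favours INT |
|---|---|---|---|
| 0 | 0 | 2.5% | 2.5% |
| 0.2 | 0.548 | 7.6% | 2.5% |
| 0.3 | 0.822 | 12.2% | 2.5% |
| 0.5 | 1.369 | 26.2% | 2.5% |
| 0.8 | 2.191 | 56.2% | 2.5% |

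A simulation of 100,000 three-arm trials at each e agreed to within 0.1 percentage points.

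**4. Effect on the later sample size, as an illustration.** For 80% power at two-sided 5%, n per arm ≈ 2(1.960 + 0.842)²/d² = 15.70/d². Suppose c = 0.5 and e = 0.3 (assumed). INT-PLA would then estimate 0.5, giving 15.70/0.25 = 62.8, or 63 per arm. INT-CG would estimate 0.8, giving 15.70/0.64 = 24.5, or 25 per arm. A placebo-controlled trial of 25 per arm with a true effect of 0.5 would have power of about Φ(0.5 × √(25/2) − 1.960) = Φ(−0.19), or about 42%.

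**The case against.** The best defence is that the authors have not ignored expectancy. They include a placebo arm with a similar-looking powder on the same ingestion schedule, and the guess question is meant to gauge how far the placebo affects the results. Nothing shows that the INT-PLA blind is broken. The choice of contrast is often left to a statistical analysis plan, which is not shown. The study is also a pilot with a convenience sample. All of this stands, and it lowers the severity. It does not make the blinding statement true, and an analysis plan could not do so either. The aim and hypothesis concern efficacy and leave the comparator open in the protocol itself.

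Three stronger readings are tempting but not supported:

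- A reader might infer that the person handing out the powder falsifies the blinding, because "The nutritionist in charge of this step will also distribute either the placebo or the CrM to the participants in each of these groups". But the protocol describes this person as "a nutritionist not otherwise associated with the study who will randomly allocate each participant to a group" and never says that they are blinded. An independent unblinded dispenser is compatible with blinded participants, staff and investigators. Coded packs and the form of the allocation list are details that an article may omit.
- A reader might infer that INT-CG will carry the conclusion. No section says so; the protocol only leaves it possible.
- A reader might infer a large overall false-positive rate from testing every pair of groups at every visit. The protocol plans a linear mixed regression for group differences, not a set of separate uncorrected tests. Such a rate would in any case measure multiplicity, not the blinding defect.

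**Conclusion.** The blinding statement is wrong as written for CG, one third of the sample, and therefore for two of the three pairwise comparisons. This follows from the protocol's own text and needs no assumption. INT versus PLA can still be blind.

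The consequence is a risk, not a demonstrated bias: with a self-rated outcome and no named comparator, an expectancy effect seen in INT-CG could be reported as a CrM effect. Its size depends on an expectancy effect that the document does not give. Over an assumed 0.2 to 0.8 SD, with no CrM effect, a significant INT-CG result favouring INT appears in about 8% to 56% of trials, while INT-PLA stays at 2.5%. The sample-size example rests on similar assumptions.

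This should be fixed. It does not invalidate the design, because the comparison that is needed is already in it.

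**What to change.** - In the abstract and in Study design, state that INT versus PLA is double blind and that CG is open, without placebo.
- In the aim, hypothesis and Statistics section, name INT-PLA as the single contrast for the conclusion about CrM and for the effect size that informs the later trial.
- Report INT-CG and PLA-CG as secondary and label them unblinded. PLA-CG then describes the expectancy effect.
- Put the week 8 treatment-guess question to PLA and INT participants only.

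The cost is a few sentences and a more modest blinding claim. The number of participants, the arms and the visits stay as they are.

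### The nutritionist who allocates participants also gives them the powder, which weakens the double-blind claim for a self-rated outcome; that claim can in any case cover only PLA versus INT

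*Protocol article*

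**What the plan says.** All the relevant text is in the Study design section of the protocol article.

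- **Size:** "The study will include a convenience sample of 45 patients", in three arms, "with 15 patients in each group".
- **Who randomises:** a nutritionist from outside the study team.
- **How:** this person is to "randomly allocate each participant to a group until the desired sample size is reached".
- **Who supplies the powder:** "The nutritionist in charge of this step will also distribute either the placebo or the CrM to the participants in each of these groups".
- **Blinding:** "the participants, staff and investigators, will be unaware of treatment group the patients are allocated to".
- **Control arm:** "CG will not receive any treatment other than usual treatment".

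The Outcomes section makes the RPQ, a self-rated symptom score, the primary outcome. The Procedure section adds that participants will be asked at week 8 which powder they believe they received.

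**The concern.** Two things in the stated procedure sit badly with the blinding statement.

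First, allocation and supply are in the same hands. Whoever assigns a participant to INT or PLA knows the group, and that person then provides the powder to the participant. Tone, remarks or answers to questions can pass on an expectation without any intent to do so. A self-rated symptom score has no independent assessor to filter that out.

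Second, the blinding statement covers the whole trial, yet one of the three arms receives no powder. CG participants know they are in CG, so comparisons with CG are not blinded to the participant who supplies the outcome.

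At stake is the reading of the INT–PLA difference, the only contrast that separates creatine from expectation. The pilot is also meant to inform a larger trial, so a weak dispensing step could be carried forward.

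**Working it through.** **1. The plan's own figure.** 3 arms × 15 = 45, which matches the stated total.

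**2. The statements side by side.**

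| Statement in Study design | What follows |
|---|---|
| The nutritionist allocates each participant | This person knows every allocation |
| The same nutritionist distributes placebo or CrM to participants | A person who knows the group deals with 2 × 15 = 30 participants |
| Participants, staff and investigators are unaware of group | True of the nutritionist only if that role is not counted as staff |
| CG receives usual treatment only | The 15 CG participants (15/45 = one third) know their group |

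The dispensing problem comes from what is written in rows 1 and 2. It does not depend on anything the article omits.

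**3. What the allocation sentence implies under different readings.** The article does not say how the random sequence is made, so three readings were worked through. Inputs are 45 participants and 3 arms of 15. Equal probability over the open arms is assumed, because no allocation probabilities are given.

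- *Independent draws, no cap.* P(15/15/15) = 45! / (15!³ × 3⁴⁵) = 0.018, or 1.8%. Summing the exact multinomial probabilities, the smallest arm is 12 or fewer with probability 0.61.
- *Independent draws, each arm closed at 15.* By simulation (30,000 runs), a mean of 3.5 final allocations are fully determined (median 3, 5th to 95th percentile 1 to 8). At least one arm is already closed for a mean of 9.5 participants.
- *One pre-made random permutation of 15/15/15.* The expected closing run of a single arm is 3 × 15/(30 + 1) = 1.45 allocations; simulation gives 1.4 (5th to 95th percentile 1 to 3). At least one arm is used up for a mean of 4.2 participants.

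Any scheme fixing 15 per arm leaves at least one determined allocation, so 1.4 is close to the floor.

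**4. Check on the form of list used in the fix.** If block sizes of 3, 6 and 9 are drawn freely and the list is cut at 45, about 33% of lists miss 15/15/15 (simulation, sizes equally likely). Mixed blocks give the stated arm sizes with certainty only if their sizes are chosen to sum to 45.

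**The case against.** An independent unblinded person who prepares or dispenses study product is an accepted arrangement. Someone not otherwise associated with the study can reasonably be read as outside the group of participants, staff and investigators who are said to be blinded. Coding of packs is a detail that a journal article may leave to the full protocol, and the week 8 question gives a partial check on unblinding.

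Much of this stands. The existence of an unblinded nutritionist is not the fault, and the article does not show that the blind would be broken. What remains is the contact: the article chose to describe the dispensing step, and it describes the allocator supplying participants. The week 8 question can show that guesses were better than chance, but it cannot undo the effect on ratings already given.

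A reader might infer two stronger things, and the documents support neither:

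- *That the stated randomisation cannot deliver 15 per arm.* The text does not say that draws are independent or that arms close at 15. A pre-made 15/15/15 list satisfies both the allocation sentence and the stated arm sizes, and sequence generation is commonly left to the full protocol.
- *That recruiters could foresee allocations.* That needs knowledge of past allocations, which the text gives only to the nutritionist, who is not said to recruit, screen or assess. Recruiters might learn who is in CG, but the two powders are described as alike in appearance, so this route does not reveal INT versus PLA.

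**Conclusion.** The point holds for dispensing and for the scope of the blinding statement. As written, one person who knows the allocation supplies all 30 powder recipients, and those recipients rate their own primary outcome. This weakens the double-blind claim, which can apply only to INT versus PLA. The conclusion assumes that distributing to participants involves contact with them, which is the plain reading. The documents give no basis for putting a number on any resulting shift in RPQ.

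The figures of 1.8%, 3.5 and 1.4 are arithmetically sound, but each belongs to one reading of the allocation sentence. They do not show a stated error. They are a reason to name a balanced list when the dispensing text is revised. Label: cheap improvement.

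**What to change.** Revise the allocation and dispensing text in Study design along these lines:

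1. Before enrolment, a random list giving exactly 15/15/15 is generated and concealed from everyone who recruits or assesses. It is either a single random permutation or mixed blocks whose sizes sum to 45.
2. The independent nutritionist packs identical containers, each with its own number, from that list.
3. Allocation is released only after the participant's baseline RPQ is complete.
4. Blinded staff hand out the containers by number, and the nutritionist has no contact with participants.
5. The double-blind statement is limited to PLA versus INT, and the article says plainly that CG is open.

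The cost is generating one list and packing and labelling for about 30 participants, with no extra staff. If a concealed balanced list and coded packs are already in the full protocol, a sentence saying so, together with items 4 and 5, is enough.
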